## Discussion

To our knowledge, this is the first multicenter RCT that compares two active psychotherapies in the early stage of bipolar disorder. We hypothesize that a specific, educational, cognitive therapy (SECT) will be superior to a supportive (EFST) group therapy regarding the time to relapse into a manic or depressive episode. The second aim of this study is to measure the effect of our interventions on other outcome parameters (social functioning) and further, to identify clinical and neurobiological predictors for successful psychotherapeutic interventions in bipolar disorders.

One limitation of the study might be the relatively new treatment format: Instead of weekly group sessions, we provide participants with four daylong workshops, mostly offered on Saturdays. This facilitates us to access and recruit a broader sample of patients living at a greater distance from the study sites. As the standard care and availability of specialized services for bipolar disorder vary significantly dependent on whether one lives in an urban or rural area, providing a therapeutic service which is accessible to a broader catchment area, is of great importance. Consequently, designing an intervention concept that is accessible to patients living far away from university hospitals and specialized service centers, which tend to be based in urban areas, reflects a unique strength of the study.

Both treatment manuals were finalized shortly before the beginning of the study and hence no data exists on the acceptance of the interventions. A pre-existing CBT manual in our group [15] has been elaborated upon by integrating elements of mindfulness and metacognitive training that had been successfully tested in a pilot study [12] in a cohort of patients with late-stage bipolar disorder. Therefore, it is conceivable that the positive effects in our pilot study cannot be generalized or replicated in a different sample. The EFST treatment manual has been developed closely in line with the one-to-one therapy manual in our previous study [17]. Although the manuals are inspired by those for individual treatment, where they proved to be effective, this does not necessarily mean that we can expect the same results in a group setting. Indeed, we cannot exclude the possibility that the group condition influences the modality of the treatment in a significant way. Furthermore, it is questionable as to whether the recruitment of patients, many of whom are already known to psychiatric services at the various study sites, implies a particularly homogenous sample: Those individuals with bipolar disorder who do not take advantage of professional medical advice or seek out psychotherapeutic support may respond to therapy in a different way.

A further concern is the within-group variability, arising from heterogeneity across the spectrum of bipolar diseases. According to previous research [37], different personality styles within major depressive disorder (MDD) have an influence on how patients respond to therapy and whether they adhere to treatment. By distinguishing two personality types within MDD, the authors have shown that patients with increased self-criticism may be inhibited by structured therapies such as cognitive-behavioral therapy. It is quite conceivable that adherence is similarly influenced by different personality types in bipolar disorder. As we compare two different forms of therapy, one more structured (SECT) than the other (EFST), without assessing the personality traits of patients, we cannot report on to what extent there may be a reciprocal influence. In addition, aspects such as variability of group size and the degree of the structure may play a more significant role and may have a negative impact on the outcome. Another limitation may arise from the uncertainty regarding whether patients, despite awareness of the exclusion criteria regarding concurrent individual psychotherapy parallel to the study, may choose to discretely engage in one-to-one therapy, which could influence the results. Furthermore, we do not assess patients’ preceding therapy experiences, which may result in within-group variability: Someone with an initial maniEFSTation and no therapy experience may respond differently to the intervention from someone with accumulated years of therapeutic care. Finally, although there have been various attempts to create uniform conditions across the various study centers, a multicenter study always bears the risk of a certain variability that cannot be ruled out completely.

One strength of our study lies in the profound experience of the authors in planning and implementing multicenter RCTs in psychotherapy with an emphasis on affective disorders. The second strength is the fact that the study is embedded in the “Network for the Research in Psychiatric Diseases” funded by the Federal Ministry for Education and Research (BMBF). This network merged the most active academic centers for bipolar disorder research in Germany with significant funding to address the research agenda. For instance, a unique electronic study platform has been established for this project. This platform has since enabled the network to improve and simplify data collection and management over the study centers which are distributed nationwide in Germany.

This accumulation of expertise and great logistical support enables us to conduct the biggest RCT in the field of psychotherapy in bipolar disorders to date. On the basis that the study is conducted across multiple sites, we have managed to recruit a large sample size and to create a setting that enables the inclusion of patients from both urban and more difficult-to-reach rural areas. With recruitment of 300 bipolar patients in remission, we are in a position to examine a wide range of scientific questions beyond our primary hypothesis, especially the search for clinical and neurobiological (fMRI) predictors for psychotherapeutic success.

## Trial status

Protocol version number: 2.0 | date: 1 September 2017.

Recruitment started on 01 August 2015; the first group of patients was randomized in November 2015. All study sites are active since October 2017. The approximate date when recruitment will be completed will be 31 December 2019. The follow-ups of study participants will end in January 2020.

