**Methods:**

In this multicenter randomized controlled trial (RCT), 300 patients with bipolar disorder are randomized to one of two group psychotherapies: Specific Emotional-Cognitive Therapy (SECT; intervention group) or Emotion-Focused Supportive Therapy (EFST; active control group). Each therapy comprises of a total of 48-h sessions (delivered once a month) over a period of 4 months. Assessments take place at baseline (t1); 6 months follow-up, i.e., post-intervention (t2); 12 months follow-up (t3); and 18 months follow-up (t4), whereby 18 months follow-up is the primary time point of interest.

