### Sample size calculation

Sample size calculations refer to a log-rank statistic under *α* = 0.05 and *β* = 0.2 (80% power) under the assumptions of (a) an accrual time of 24 months, (b) a total study duration of 48 months with a primary time point of interest at 18 months post-baseline, and (c) a drop-out rate of 12% (the latter based on experiences from previous studies [2, 3, 5]; and relates to the study observation period of 18 months). We define a treatment effect of factor 2 as a relevant effect, i.e., a hazard ratio (HR) of 0.5, for instance, is regarded as a relevant effect. Previous trials have indicated about 4% of the study population under risk (excluding dropouts) will experience a relapse under conventional therapy each month. HR = 0.5 would require 2% per month for the SECT group and a study population of *N* = 360 patients (180 patients per treatment arm) to reach significance under *α* = 0.05 and *β* = 0.2. The study with a proposed *N* = 300 would require HR = 0.46, and the pessimistic scenario of *N* = 200 would have to reach HR = 0.375. Thus, the study with *N* = 300 intended can yield statistical significance if the treatment effect in the SECT group exceeds factor 2. In addition, our sample size calculation is based on the publication by Jahn-Eimermacher et al. [33] which fits—regarding sample sizes for time-to-event data—the requirements of the present study best and results in an identical sample size.

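### Recruitment to 31 December 2019 with follow-up ending in January 2020 cannot be squared with an 18-month primary time point

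*Protocol article*

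**What the plan says.** The Trial status section gives the calendar. On the start: "Recruitment started on 01 August 2015; the first group of patients was randomized in November 2015". On the sites: "All study sites are active since October 2017". On the end, in two adjacent sentences: "The approximate date when recruitment will be completed will be 31 December 2019. The follow-ups of study participants will end in January 2020".

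The design sections give the follow-up per patient. The Abstract says that "18 months follow-up is the primary time point of interest". Design and procedure puts t2 at month 6, t3 at month 12 and t4 at month 18, with an intervention of up to 5 months between t1 and t2. Assessments/measures repeats the 18-month primary time point, counted from baseline, and Table 1 there places the intervention in months 2 to 5. The Sample size calculation section assumes "an accrual time of 24 months, (b) a total study duration of 48 months with a primary time point of interest at 18 months" post-baseline, with 12% dropout over those 18 months.

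**The concern.** If recruitment closes one month before follow-up stops, a patient who enters late cannot be observed for 18 months. The calendar and the visit schedule then describe two different trials, and a reader cannot tell which will be run.

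If the calendar is followed, three things are at stake:

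- Relapse status at month 18 is unknown for late entrants unless they relapse before the cut-off.
- The secondary outcomes at t3 and t4 (functioning, symptoms, missed days) are not collected for them. These are planned for ANCOVA over two to four time points, which has no censoring mechanism.
- The Statistical analysis section plans to compare patients with and without the primary outcome at the primary time point, by arm. Late entrants would fall into the missing groups beside true dropouts, and that comparison would mix entry date with attrition.

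The person-time lost is mostly after therapy, which is the period a relapse-prevention trial is meant to observe.

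**Working it through.** **Plan's own figures.** The article gives no end-of-study event count or accrual curve, so there is no stated figure for the affected share to reproduce. The stated N = 360 for a hazard ratio of 0.5 could not be reproduced: two-sided Schoenfeld needs 66 events, and with 51.3% and 30.2% relapsing by month 18 that gives 162 patients, or 162/0.88 = 184 with dropout. That is a separate matter. It does mean that the power figures below come from the stated rates, not from the plan's own calculation.

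**Step 1: calendar (no assumption needed).**

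- 31 December 2019 + 18 months = 30 June 2021, the t4 date of the last patient.
- January 2020 − 18 months = July 2018 (1 to 31 July, by the day in January), the last enrolment that permits t4.
- Recruitment after that point: 17 to 18 months.
- 31 January 2020 − 5 months = about the end of August 2019 (the start of August if follow-up stops on 1 January). Later entrants cannot complete a 5-month intervention period before follow-up stops.
- A patient enrolled in late December 2019 is about 1 month past baseline at the end of January 2020, before the month 2 to 5 window opens.

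**Step 2: share of patients (accrual pattern assumed).** The accrual period is 53 months from 1 August 2015, or about 50 from November 2015.

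- Uniform: 17/53 = 32% at the low end; 18/50 = 36% from 1 November 2015, and 37% if the first randomisation was at the end of that month. That is about 96 to 110 of 300.
- Accrual rate rising linearly from zero: 1 − (36/53)² = 54%.
- Accrual rate falling linearly to zero: (17/53)² = 10%.
- Accrual before October 2017 at 75%, 50% or 25% of the later rate: about 37–38%, 43–44% or 51–52%.
- Accrual after July 2018 at half or a quarter of the earlier rate: about 19–20% or 11%.

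For other visits, from 1 August 2015 with a cut at 31 January 2020:

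| Accrual | Short of month 18 | Short of month 12 | Short of month 6 |
|---|---|---|---|
| Uniform | 32% | 11/53 = 21% | 5/53 = 9% |
| Linear ramp | 54% | 1 − (42/53)² = 37% | 1 − (48/53)² = 18% |

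**Step 3: events and power at N = 300.** Inputs from the Sample size calculation section: relapse 4% and 2% per month (hazard ratio 0.5), 12% dropout over 18 months. The type I error is taken as two-sided 0.05; the article does not state sidedness.

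- Dropout hazard d = −ln(0.88)/18 = 0.0071 per month.
- Relapse probability over follow-up f: λ/(λ+d) × [1 − exp(−(λ+d)f)]. At f = 18 this is 0.485 (λ = 0.04) and 0.285 (λ = 0.02).
- Full follow-up: 150 × (0.485 + 0.285) = about 116 events.
- Replacing f by the smaller of 18 and the time to 31 January 2020, averaged over entry dates from 1 August 2015: about 100 events (uniform) or 88 (ramp), a loss of 13% to 24%.
- Power = Φ(√(events/4) × ln 2 − 1.96): 0.96 with 116 events, 0.93 with 100, 0.90 with 88.

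Uniform accrual from November 2015 with a flat 12% deduction gives 108 falling to 92 events, power 0.95 to 0.91, and mean follow-up 18 to 15.1 months.

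**The case against.** The strongest reply is that January 2020 is a slip. A one-month gap leaves the last entrants no time even for therapy, so it is hard to read as deliberate, and the 18-month design is consistent everywhere else. This is plausible. It explains the contradiction but does not remove it, because nothing in the article shows which date is wrong.

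The second reply is that a log-rank analysis handles late entry by administrative censoring. That stands for time to relapse, and the power loss is modest. It does not help 18-month status, the t3 and t4 secondary outcomes or the missing-outcome comparison.

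Some stronger readings are tempting but not supported:

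- A reader might infer that a third or more of patients are affected. That needs uniform or back-loaded accrual. Activation of all sites only by October 2017 makes front-loading less likely, but no accrual by date is given, and the Discussion speaks of a large sample as already recruited.
- A reader might infer that the latest entrants get no therapy. The section dates the end of follow-up, not of therapy. Only completion within the follow-up period is ruled out.
- A reader might say that the event count falls below the one the trial was sized on. No such count is stated.
- A reader might hold that 24 and 48 months contradict the actual calendar. Those are planning assumptions, and slower accrual does not make them wrong.

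**Conclusion.** The point holds as an internal inconsistency. Recruitment to about 31 December 2019, follow-up ending in January 2020 and an 18-month primary time point for all patients cannot all be true. This rests on dates alone.

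Everyone enrolled after about July 2018 would miss month 18. How many that is depends on an undocumented accrual pattern, so the range in step 2 is conditional and no single percentage should be cited as the plan's. The patients so lost are additional to the dropout allowance, which covers attrition only.

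The harm lies in unobserved 18-month status and missing later secondary outcomes more than in lost power for the log-rank test. The power figures assume the stated relapse rates, constant hazards and a hazard ratio of 0.5 throughout. They would not carry over if the treatment difference emerged mainly after therapy.

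**What to change.** Reconcile the dates in the Trial status section with the visit schedule, in one of three ways:

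1. State that follow-up ends when the last randomised patient completes t4, about 30 June 2021 if recruitment closes on 31 December 2019.
2. If January 2020 is a hard stop, state the last enrolment date that permits month 18, about July 2018.
3. Failing both, declare administrative censoring at the stop date, keep it separate from dropout in the missing-outcome comparison, and restate expected follow-up, events and power under the accrual calendar adopted.

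If January 2020 is a slip, the cost is a corrected date. Otherwise the first option costs a longer calendar for visits already promised to each patient, with no new patients or procedures. The second shortens recruitment and may leave the sample below 300. The third costs a short recalculation and accepts the missing 18-month data.

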## Data Availability

The data is not available until the main results are published.

## Abbreviations

ASRM: Altman Self-Rating Mania Scale
CBT: Cognitive behavioral therapy
DGBS: Deutsche Gesellschaft für Bipolare Störungen
EFST: Emotion-Focused Supportive Therapy (German term: Fördernde Emotionsfokussierte Supportive Therapie)
GAF: Global Assessment of Functioning
HR: Hazard ratio
ITT: Intent-to-treat group
LIFE: Longitudinal Interval Follow-up Evaluation
MWT: Mehrfachwahl-Wortschatz-Intelligenztest
PP: Per-protocol group
PI: Principal investigator
QIDS-C: Quick Inventory of Depressive Symptomatology clinician form
QIDS-SR: Quick Inventory of Depressive Symptomatology self-report form
SAEs: Serious adverse events
SCID: Structured Clinical Interview for DSM
SECT: Specific Emotional-Cognitive Therapy (German term: Spezifische Emotional-Kognitive Therapie)
YMRS: Young Mania Rating Scale
